### Recruitment

Recruitment of potential participants will occur by a review of medical records of the women who delivered babies in the research sites. Potential participants who meet inclusion criteria will receive a phone call from a trained project field officer to explain the purpose of the study and assess interest in participation. The trained project field officers who are physicians or nurses working in the research sites will be recruited from the research sites.

The project field officers will confirm their eligibility and obtain consent. As part of eligibility assessment, all interested study participants will undergo postpartum HbA1c testing to make sure the potential subjects do not have T2DM. If HbA1c suggests T2DM, the participant will not be eligible to participate in the study. However, she will be referred to the physicians for further T2DM diagnosis and treatment. If HbA1c are within normal limits, the women will be recruited. Women who do not meet the inclusion criteria will be thanked for their time. We will also document reasons from mothers who decline to participate in the study.

### Intervention

Participants will be enrolled in the study for a total of 18 months. For both groups, the assessment time points include at the beginning of the study (T-0), at 3, 6, and 18 months after baseline assessment (T-1, T-2, and T-3). The 3-, 6- and 18-month after baseline assessment include questionnaires completion as T-0 and the physical assessment (e.g. BMI, waist circumference, blood pressure, OGTT-2 h, and HbA1c). If the OGTT-2 h is abnormal at any time point, the next time point the participants will not assess OGTT-2 h. The timeline of the intervention activities for ILSM group and control group is showed in Table 1.

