### Variables and measurements

Each measure was selected to operationalize theoretical constructs and has been used in Chinese rural populations and demonstrated adequate psychometric properties. The research team will measure outcomes at baseline (T-0), immediately after main ILSM at 3 months (T-1), immediately post intervention at 6 months (T-2) and 18-month post intervention (T-3), which are displayed in Table 3. All measures employed in the proposed study will be collected by trained research assistants who are blinded to the group assignments.

**Table 3 Tab3:** Variables and measures collected at evaluation time points

Variables		Data source	Measures	Time point			
				T-0	T-1	T-2	T-3
Covariates	Socio-demographic factors	Survey & medical record	Age, marital status, education level, occupation, annual household income, and ethnicity.	×			
	Health characteristics		Smoking status, alcohol consumption, pre-pregnancy BMI, gestational weight gain, parental history of diabetes, GDM, and cardiovascular disease.	×			
	Clinical characteristics		Gestational week and age at the diagnosis of GDM, numbers of pregnancies, history of pregnancy complications, birth weight of children, gestation week at delivery, treatment for GDM.	×			
Weight-related Behaviors	Dietary intake	Survey	Food frequency questionnaire [40]	×	×	×	×
	Physical activities		International Physical Activity Questionnaire (Short version) [41]	×	×	×	×
Psychosocial Variables	Self-efficacy: the belief in one’s effectiveness in performing specific tasks.	Survey	Self-rated abilities for health practices scale [42]	×	×	×	×
	Perceived stress: the feelings or thoughts that an individual has about how much stress they are under over a given time period.		Perceived Stress Scale [43]	×	×	×	×
	Social support: the perception and actuality that one is cared for.		Social Support Rating Scale [44]	×	×	×	×
	Quality of life: the general well-being of individuals		The World Health Organization Quality of Life Scale-BREF [45]	×	×	×	×
Physiological outcomes	Insulin resistance: a physiological condition in which cells fail to respond to the normal actions of the hormone insulin	Spot measuring	OGTT-2 h	×	×	×	×
	T2DM screening & development		HbA1c ≥6.5% is considered T2DM.				
Weight-related measures	BMI & Waist circumference	Spot measuring	BMI is weight/height^2^ (Kg/m^2^)	×	×	×	×
Cardiovascular disease risk	Blood Pressure	Spot measuring	Systolic blood pressure, Diastolic blood pressure	×	×	×	×

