Cost-effectiveness Outcomes	The costs falling on health and social care systems	Survey & Medical records	A PI-designed questionnaire	×	×	×	×
	The costs falling on individuals and families						
	The effectiveness outcomes		The above clinical and physiological measurements	×	×	×	×

Personal and family characteristics (Covariates): Socio-demographic factors, health characteristics, and clinical characteristics will be collected. Weight-related behaviors (Secondary outcome measures): Two separate questionnaires on changes in dietary intake and physical activity habits will be assessed. Psychosocial variables (Secondary outcome measures): self-efficacy, perceived stress, social support, and quality of life will be measured, the operation definition of which are displayed in Table 3. Physiological outcomes: BMI and waist circumference will be measured as weight-related variables, while blood pressure will be evaluated as cardiovascular disease risk. The biomarkers of insulin resistance will include glucose values on the oral 75 g glucose 2 h post-load glucose tolerance test (OGTT-2 h). T2DM screening and development will be measured by HbA1c. BMI, OGTT-2 h, and HbA1c are the primary outcome measures.

Cost-effectiveness outcomes: We will measure the costs accruing to the health and social care system and to individuals and families for the ILSM program and for health care (in order to assess the effects of ILSM), including inpatient and ambulatory care, medicines, personnel costs to deliver the ILSM, and other procedures and treatments. For the effectiveness component, we will rely on clinical and physiological measurements noted above. These two elements permit cost-effectiveness calculations. In addition, we will assess the costs falling on individuals and families for non-medical costs (travel, child-minding, and time/lost income), which will be used in a secondary cost-effectiveness calculation.

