### Statistical analysis

Our analysis plan focuses on comparisons between ILSM and control groups with respect to key intermediate outcomes: HbA1c (%),OGTT 2 h (mmol/L), BMI, waist circumference (in cm), SBP and DBP (mmHg), and measures of dietary intake, physical activity, self-efficacy, and social support. The comparisons take the form of 1) simple differences of average values of change (for quantitative characteristics) from baseline to follow-up measures or turnover tables showing baseline versus follow-up (for data organized into categories) and 2) more complex analyses based on multivariate methods that incorporate adjustment for clustering and covariates.

We will assess cost-effectiveness using an existing spreadsheet-based simulation model called GeDiForCE (Gestational Diabetes Formulas for Cost-Effectiveness), developed by UCSF and Health Strategies International with funding from NovoNordisk. This model uses a decision tree and input values from published studies to portray the risks of T2DM with and without a post-partum intervention. In this study, we will adjust input values to reflect data collected on costs and effectiveness. The cost data described above can be directly incorporated into the model. The effectiveness data will be calculated from the clinical and physiological outcomes above. We will directly incorporate incidence of T2DM. However, due to the relatively short follow-up time frame, as compared with a delay of ten or more years for the incidence of T2DM, we will also use short-term changes in physiological indicators (such as OGTT-2 h and HbA1c) in a simple risk-of-progression model in order to predict long-term effects on incidence of T2DM. This progression model will be calibrated to empirical evidence on the progression from glucose intolerance to T2DM.

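### OGTT-2h, a primary outcome, is skipped at the visit after an abnormal result although Table 3 schedules it at every visit, so observed OGTT-2h results describe a selected subset

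*Protocol article*

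**What the plan says.** All references are to the protocol article.

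- **Intervention.** Follow-up is at 3, 6 and 18 months (T-1, T-2, T-3). Each visit includes "the physical assessment (e.g. BMI, waist circumference, blood pressure, OGTT-2 h, and HbA1c"). The text then adds: "If the OGTT-2 h is abnormal at any time point, the next time point the participants will not assess OGTT-2 h". Abnormal is not defined. Any time point includes baseline.
- **Variables and measurements.** "BMI, OGTT-2 h, and HbA1c are the primary outcome measures". In Table 3 the insulin resistance row ("a physiological condition in which cells fail to respond to the normal actions of the hormone insulin"), measured by OGTT-2h, is marked at all four time points with no exception for an earlier abnormal result.
- **Recruitment.** Entry is screened on HbA1c alone: "If HbA1c are within normal limits, the women will be recruited". A woman with an abnormal baseline OGTT-2h can therefore be enrolled and meet the rule at once.
- **Statistical analysis.** The first comparison named is "simple differences of average values of change (for quantitative characteristics) from baseline to follow-up measures", or baseline-by-follow-up turnover tables for categories. The second is a set of multivariate methods adjusted for clustering and covariates. How a skipped OGTT-2h enters either is not stated.

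**The concern.** The rule leaves a primary outcome unmeasured because of its own previous value. The women not measured are those with the worst last result. Two consequences follow from the text alone, whatever the cut-off:

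- No woman abnormal at T-0 has a T-1 value. The abnormal row of the T-0 to T-1 turnover table is empty by design, so the trial cannot observe reversion to normal at 3 months.
- A woman abnormal at T-0 is skipped at T-1 and tested again at T-2. She has a T-3 value only if her T-2 result was normal. Her row at 18 months is filled only by women who had already improved.

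At stake are the reported OGTT-2h levels, the proportions above threshold, the within-arm changes, and part of the information on a primary outcome. From T-2 onward the share skipped also depends on treatment, if ILSM changes the abnormal rate.

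**Working it through.** **The plan's own figure.** The article gives no expected share of skipped tests. Its only design figure on OGTT-2h is power of about 0.71 with N = 256. That figure does not enter this point.

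**Inputs not in the documents (assumed).** OGTT-2h is normal with mean 7.0 and SD 1.7 mmol/L. Abnormal means 7.8 or more. The between-visit correlation r is 0.4 to 0.8. The true ILSM effect is -0.3, -0.6 and -0.6 at T-1, T-2 and T-3.

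**Step 1: share skipped at T-1.** z = (7.8 - 7.0)/1.7 = 0.47, so 1 - Phi(0.47) = 0.32. That is about 0.32 x 256 = 82 women. For means of 6.5 and 7.5 the share is 22% and 43%. It depends only on the pre-treatment value, so it is equal between arms in expectation.

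**Step 2: apparent control change at T-1 (true value 0).** Among women normal at baseline, the expected change is (1 - r) x SD x phi(z)/Phi(z), and 1.7 x 0.357/0.681 = 0.89.
- r = 0.4: 0.6 x 0.89 = +0.53
- r = 0.6: 0.4 x 0.89 = +0.36
- r = 0.8: 0.2 x 0.89 = +0.18

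Simulation gives +0.17 to +0.54. This is regression to the mean. It affects both arms alike, so the T-1 mean contrast stays at -0.30.

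**Step 3: T-3, by simulation of the rule** (four visits, several hundred thousand women per arm; ranges are over r, and runs differ by about 0.01).

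| Quantity at T-3 | True | Observed under the rule |
|---|---|---|
| Missing, control | 0% | 26-28% |
| Missing, ILSM | 0% | 17-19% |
| Controls above threshold | 32% | 16-26% |
| Difference in raw means | -0.60 | -0.53 to -0.43 |
| Difference in change from baseline | -0.60 | -0.62 to -0.64 |
| Threshold OR, effect persists | 0.55 | 0.57-0.58 |
| Threshold OR, effect gone by T-3 | 1.00 | 1.08-1.32 |

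With 128 per arm (equal arms assumed), 92-95 controls and 104-106 ILSM women have a T-3 value. That is 196-201 of 256.

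Raw means are attenuated by 12-28% (1 - 0.53/0.60 to 1 - 0.43/0.60). Change from baseline is exaggerated by 3-7% (0.62/0.60 to 0.64/0.60).

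**Step 4: sensitivity.**
- No effect at any visit: missingness is equal between arms and the contrasts stay near zero.
- Cut-off 11.1 mmol/L: z = 4.1/1.7 = 2.41, so 0.8% are skipped at T-1. Under 1% are missing at every visit, and bias in the mean contrasts is at most about 0.02.
- Other assumptions (SD 1.8, means 6.5 to 7.8, constant effect -0.45, cut-off 7.8): T-3 missing is 19-45% of controls and 14-38% of ILSM. Raw means give -0.31 to -0.41, and change from baseline gives -0.46 to -0.53. The pattern is the same.

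**Step 5: does the proposed model work?** A mixed model on all observed values returned -0.61 (true -0.60), and +0.02 (true 0) when the effect had faded. Maximum likelihood under the second set of assumptions recovered about -0.45 (true -0.45).

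**The case against.** The strongest reply has four parts.

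1. *The bias in the stated arm comparison is small.* This stands. The article names change from baseline, and that contrast is off by only 3-7% at T-3, in the direction of exaggeration. Even when the effect has faded by T-3 it is about -0.04. The larger attenuation belongs to raw T-3 means, which the article does not name. The OR of 1.08-1.32 needs a -0.6 effect at T-2 that vanishes completely by T-3.
2. *Everything depends on an undefined cut-off.* This stands for the size. It does not rescue the text: the empty turnover row follows for any cut-off, and the size cannot be known until abnormal is defined.
3. *Handling of missing data belongs to the analysis plan, which is not shown.* This stands in part. The multivariate methods could be likelihood-based, and nothing commits the trial to observed cases only. But the skip is a data-collection rule fixed in the protocol, and no analysis plan can restore a test that was not done.
4. *Table 3 merely lacks a footnote.* Possibly. Even so, a site following Table 3 and a site following the Intervention text would collect different primary-outcome data.

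The Usual care section is not a further contradiction. It says controls have the same measurements at the same intervals, and the skip rule applies to both arms.

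**Conclusion.** The point holds as a conflict between the Intervention text and Table 3, and as a rule that makes the observed OGTT-2h data selective. With abnormal at 7.8 mmol/L and the other assumed values, about a third of women have no T-1 value. At T-3 the observed proportion of controls above threshold is 16-26% against a true 32%, and the loss there is about 9 percentage points higher in controls (26-28% against 17-19%).

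A reader might infer three stronger claims that the documents do not support:

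- *That the rule always loses more women from the arm doing worse.* The largest loss, at T-1, is balanced. Imbalance begins at T-2 and only if ILSM has an effect.
- *That the treatment effect is necessarily diluted.* The direction depends on the analysis, and the named change-from-baseline contrast moves slightly the other way.
- *That the rule produces false positives.* With no effect at any visit there is no bias.

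BMI, HbA1c and T2DM defined by HbA1c are untouched. This should be fixed, but the trial does not stand or fall on it.

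**What to change.** 1. Reconcile the Intervention text with Table 3 and define abnormal. Whether a skip is needed, and for whom, is for the clinical team.
2. For any OGTT-2h values still skipped, replace observed-case change and turnover comparisons as the main OGTT-2h analysis. Use a likelihood-based repeated-measures model on every OGTT value, including the abnormal one that triggered the skip, with arm-by-visit effects and a town random effect.
3. For the above-threshold analysis, multiply impute skipped values from earlier OGTT-2h, same-visit HbA1c, BMI and arm.
4. Report skipped tests by arm and visit.

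The cost is modest extra analysis work and wording. If the skip is narrowed, some tests already in Table 3 are simply done. The model relies on missing at random given OGTT history, which is reasonable because the skip depends on a recorded value. It also relies on the model form: no woman abnormal at baseline has a T-1 result, so her T-1 value is inferred from her other visits and cannot be checked directly.

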**Table 1 Tab1:**
[figure not shown]
Intervention activities timeline

ILSM (Intervention):

The ILSM program is guided by the Social Cognitive Theory (SCT) which has been widely applied to the health-promotion and preventive behaviors, and risky lifestyles [31, 32]. The ILSM program is designed to improve behavioral (dietary intake & physical activities), psychosocial (self-efficacy, perceived stress, & social support), physiological outcomes [Hemoglobin A1c (HbA1c), OGTT 2 h, body mass index (BMI), waist circumference, &blood pressure], and psychosocial outcome [quality of life]. Improvement in outcomes will decrease risk of T2DM and health care costs. Figure 1 displays the Social Cognitive Theory model and the proposed intervention.

**Fig. 1 Fig1:**
[figure not shown]
Social Cognitive Theory for Intensive Lifestyle Modifications on Women with prior GDM

The ILSM program includes three major components: 1) six bi-weekly in-person group sessions, 2) five bi-weekly telephone consultation sessions, and 3) 3 monthly telephone consultations to encourage behavior change. The ILSM participants who attend bi-weekly in-person sessions at the research sites provided by project field officers will also receive the bi-weekly telephone consultations from them. The time commitment is about 90 min for each in-person session and 20 min for each telephone consultation. The six in-person sessions are group sessions with 10–20 participants. Each participant will receive a brochure of diabetes prevention education information developed by the research team, including diabetes risk factors, healthy eating, exercise, and stress management.

#### Six bi-weekly in-person group sessions

The in-person sessions of ILSM program include six topics on 1) orientation and goal setting, 2) healthy eating patterns, 3) physical activities, 4) stress management, 5) family support on ILSM & family lifestyle patterns, and 6) farewell and relapse prevention. The content of ILSM program sessions are shown in Table 2. Child-care, air-conditioning room, necessary transportation, healthful snacks, and drinks will be provided in each in-person session.

**Table 2 Tab2:** The topics and content of the six group sessions of the ILSM group

Topics	Content
1st: Orientation and Goals-setting (90 min)	a. Introduction to ILSM. b. Assess personal risk of developing T2DM. c. Inform the life-threatening outcomes of having T2DM. d. Give good examples of T2DM prevention by lifestyle modification. f. Tell and ask the benefits of and barriers to lifestyle change. g. Set goals to achieve and maintain a healthy lifestyle pattern after 3 months. h. Group exercise (30 min).
2nd: Healthy eating patterns (90 min)	a. Assess current eating patterns. b. Summarize the barriers of changing unhealthy eating patterns from the previous two sessions. c. Low Glycemic Index diet. d. Analyze the barrier on dietary and solutions from the previous sessions. e. Help make individual action plan and coping plan on healthier eating patterns. Action plan: What unhealthy eating patterns would you like to change? Pattern 1, 2. For Pattern 1, When? How? Coping plan: Which barrier might prevent you from changing the eating pattern? Barrier 1, 2. How could you overcome this barrier? For Barrier 1, Strategy 1. f. Group exercise (30 min).
3rd: Physical activities (90 min)	a. Assess current physical activities. b. Summarize the barriers of performing physical activities. c. Analyze the barrier’s solutions from the previous sessions. d. Encourage raising more barriers and solutions. e. Help make individual action plan and coping plan on physical activities. Action plan: Which kind of physical activity would you like to perform? Activity 1, 2. For activity 1, When? Where? How long? Coping plan: Which barrier might prevent you from being active at least 2 × 20 min per week? Barrier 1, 2. How could you overcome this barrier? For Barrier 1, Strategy 1. f. Ask to perform aerobics together guiding by a popular DVD disk. g. Group exercise (30 min).
4th: Stress management (90 min)	a. Assess the current stress. b. Stress management: Impact of stress on feelings and behaviors and health; Identify sources of stress; Identify unhelpful stress-management strategies; Discuss more helpful ways of managing stress c. Help make individual action plan and coping plan on mental health management. Action plan: Which kind of strategy would you like to perform to reduce stress? Activity 1, 2. For activity 1, When? Where? How long? Coping plan: Which barrier might prevent you from managing stress? Barrier 1, 2. How could you overcome this barrier? For Barrier 1, Strategy 1. d. Ask to practice some psychological therapy (such as relax exercise) in groups. e. Group exercise (30 min).
5th: Family support on ILSM & family lifestyle patterns (90 min)	a. Assess the current family support on ILSM & family lifestyle patterns (meal-planning and exercise pattern) of each participant family. b. Family healthy eating: Healthier family meal-planning; Dealing with barriers to making healthier choices; Communication strategies c. Family exercise patterns: Importance of family exercise patterns; Suggestions and good examples of family exercise patterns d. Help make family action plan and coping plan with family members, on family support and family lifestyle pattern improvement. e. Ask each family member to express their intentional support to the participant. f. Group exercise (30 min).
6th: Fare well and Relapse prevention (90 min)	a. Assess the current lifestyle and relapse events. b. Relapse prevention: The principle trend phases of behavior changing, Problem-solving strategies for maintaining a healthier lifestyle; Weight and energy balance; Managing relapses c. Emphasize the importance of T2DM screening every six months d. Fare-well and conclusion for the group meeting sessions. e. Group exercise (30 min).

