#### Usual care (Control group)

Because women with prior GDM are at high risk for T2DM, it is not ethical to provide no treatment. Currently, the clinical guidelines for T2DM prevention include providing information for T2DM prevention to high risk populations, including lifestyle modification and diabetes screening (38). The usual care provided in this proposed project will utilize current clinical guideline and recommendations for T2DM prevention. Each participant will receive the same brochure of diabetes prevention education information as the ILSM group. However, participants in the control group will not have group sessions and phone consultations.

Similar to the ILSM group, four local health workers in the usual care group will be trained as the project field officers. Their responsibilities will include: (1) identify the eligible participants and recruit the participants; (2) ensure participants in the usual care group will receive general oral and written information about awareness of diabetes, information about the importance of dietary modification and physical activity, and suggestions of diabetes screening every three years at the baseline assessment; (3) make the telephone reminders and the site arrangement for the four time-points assessments. The participants will complete the same measurement at the same time intervals at the ILSM groups.

Upon completion of the 18-month study, participants from either the control group or the ILSM group will receive a 100 RMB gift certificate as “thank you” for participation and to sustain their involvement in the study. We will send all participants in this study a birthday message for her birthday. The study flowchart was displayed in Fig. 2.

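### Screening advice differs by arm (six-monthly versus three-yearly), and a T2DM rule based on visit HbA1c alone can miss women diagnosed and treated outside the trial, more often in ILSM

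*Protocol article*

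**What the plan says.** Table 2 of the protocol article lists, under the sixth group session, "Emphasize the importance of T2DM screening every six months". Under Usual care (Control group), field officers are to give "suggestions of diabetes screening every three years at the baseline assessment". The same section says that "The usual care provided in this proposed project will utilize current clinical guideline and recommendations for T2DM prevention". The article does not explain why the two arms hear different intervals.

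Testing by the trial itself is common to both arms. The Intervention section states: "For both groups, the assessment time points include at the beginning of the study (T-0), at 3, 6, and 18 months after baseline assessment". The usual-care section adds: "The participants will complete the same measurement at the same time intervals at the ILSM groups". Variables and measurements has all measures collected by research assistants blinded to group, and names BMI, OGTT-2 h and HbA1c as primary outcome measures.

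The case definition in Table 3 is "HbA1c ≥6.5% is considered T2DM". For the economic model, the Statistical analysis section states: "We will directly incorporate incidence of T2DM". Ambulatory care, medicines and other procedures are costed at all four time points from survey and medical records.

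**The concern.** The advised interval differs six-fold (36/6 months). The advice can act on the outcome by a route other than diet or activity. A woman who has herself tested between visits may be diagnosed, start treatment and reach the 18-month visit with HbA1c below 6.5%. The rule in Table 3 then counts her as free of T2DM, although she is a known case. If women act on what they are told, this happens more often in ILSM.

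Three results are exposed. T2DM development would be undercounted in ILSM. HbA1c and OGTT-2 h at 18 months would include treated values, more of them in ILSM. The cost per T2DM case averted would use that incidence directly, and would also carry the cost of the prompted tests.

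**Working it through.** The plan gives no figure on this point, so there is none to reproduce. The check counts the tests that the advice implies and then asks how far masked cases could move the T2DM comparison.

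**1. Inputs from the article.** Advice: every 6 months (ILSM, session 6) and every 36 months (control, baseline). Trial tests: months 0, 3, 6 and 18 in both arms. Follow-up: "Participants will be enrolled in the study for a total of 18 months". The longest gap between trial tests is 18 − 6 = 12 months. (Variables and measurements labels the last visit 18 months post intervention. A later visit would only lengthen the gap.)

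**2. Outside tests implied in the gap.**
- ILSM, counted from session 6: six bi-weekly sessions put it at about week 10, or 10/4.345 = 2.3 months. Tests fall at months 8.3 and 14.3, so two.
- ILSM, counted from month 3: months 9 and 15, so two.
- ILSM, counted from baseline: months 6, 12 and 18, of which only month 12 lies inside the gap, so one.
- Control: 36 > 18, so none.

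**3. Share of ILSM cases masked (assumptions).** Assume onset is uniform over 18 months, half of women take up the advice, and half of those found are below 6.5% at month 18.
- One test at month 12 reaches onsets in months 6 to 12: 6/18 = 33%. Masked share = 0.333 × 0.5 × 0.5 = 8.3%.
- Two tests, the last at about month 14.5: (14.5 − 6)/18 = 47%. Masked share = 0.472 × 0.25 = 11.8%.
- A masked share of 20% needs uptake × control of 0.20/0.333 = 0.60 with one test, or 0.20/0.472 = 0.42 with two.

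**4. Apparent odds ratio with no true effect.** With true incidence p in both arms and masked share m in ILSM,

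OR = [p(1 − m)/(1 − p(1 − m))] / [p/(1 − p)].

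An equal split of 256 is assumed (128 per arm), and p = 0.10 is an assumption, giving 12.8 true cases per arm.

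| m | ILSM proportion | ILSM cases counted | OR |
|---|---|---|---|
| 8.3% | 0.0917 | 11.7 | 0.91 |
| 11.8% | 0.0882 | 11.3 | 0.87 |
| 20% | 0.0800 | 10.2 | 0.78 |

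The ratio hardly depends on p. At p = 0.03, m = 8.3% gives 0.0283/0.0309 = 0.91 and m = 20% gives 0.0246/0.0309 = 0.80. The number of women does depend on p: m = 20% is 2.6 women at p = 0.10 and 0.8 at p = 0.03.

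**5. Mean HbA1c at 18 months.** Shift = share newly diabetic in the gap × uptake × fall on treatment. With assumed ranges of 1% to 10%, 50% to 100% and 0.5 to 1.5 points, it runs from 0.01 × 0.5 × 0.5 = 0.0025 to 0.10 × 1 × 1.5 = 0.15 points. The upper end takes every factor at its maximum.

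**6. Direction.** Steps 3 and 4 hold only if visit HbA1c alone defines a case. If outside diagnoses were counted without further adjustment, women diagnosed outside on other criteria, or who miss the last visit, would be added to the count, again mostly in ILSM. The error would then run against ILSM.

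**The case against.** The trial compares a program with usual care, and the screening message is listed as content of that program. On that reading the difference is part of the contrast under test. What is at issue is then attribution (lifestyle or screening), not bias between packages, and giving both arms the same advice would alter the intervention or the comparator. This stands: equal advice is a trade-off, not the correction of an error. The article does not say that the message is an intended active component, however, and the package reading does not make a treated case a non-case.

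A reader might infer that detection of T2DM differs between arms in general. The documents do not support that. The tests, visit times and blinded collection are common to both arms, so only diagnoses made between visits can differ, and only if women act on the advice. The Discussion reports fear of diagnosis and low risk perception among women who refused the program, so high uptake cannot be presumed.

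A reader might also infer that the artefact could exceed the planned effect: masking one third of ILSM cases gives 0.0667 against 0.10, an odds ratio of 0.64, beside the 0.667 in the power paragraph. This does not hold. One third is near the ceiling: with one test at month 12 it needs full uptake, treatment and control. The 0.667 concerns insulin resistance above a threshold with equal odds in the control group (about 50%), a different endpoint from T2DM at 10%.

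On cost, medicines and ambulatory care are already collected, and screening prompted by ILSM is properly an ILSM cost. That also stands. What remains is to show it separately. Detailed event rules may sit in a fuller document, but the case rule that the article does state can miscount by arm.

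**Conclusion.** The point holds in a limited form. The advice differs by arm as quoted, and over the 12-month gap before the last visit it implies one or two outside tests in ILSM and none in control. Combined with a T2DM rule based on visit HbA1c, it can turn known cases into non-cases, more often in ILSM. It can also put treated HbA1c and OGTT-2 h values into the primary comparison.

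The effect is probably small: an apparent odds ratio of about 0.91 to 0.78 with no true effect, or roughly one to two and a half women of 128 (12.8 × 0.083 = 1.1; 12.8 × 0.20 = 2.6). This rests on assumed 10% incidence, uniform onset, partial uptake and an equal split. It favours ILSM only while visit HbA1c alone defines a case. The finding does not show that ascertainment at trial visits is biased.

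**What to change.** - Reconcile Table 2 (sixth session) with the usual-care section, or state that the different screening advice is an intended part of the ILSM package. The interval itself is for the clinical investigators.
- In both arms, record outside tests, diagnoses and glucose-lowering medicines at each visit, using the existing cost questionnaire and medical records.
- Count a confirmed outside diagnosis or start of glucose-lowering treatment as a T2DM event whatever the visit HbA1c, with a sensitivity analysis on visit HbA1c alone. The two results together show how far the counting rule matters.
- Show the cost of outside screening as a separate line, so that cost per case averted can be read with and without it.

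The cost is a few questionnaire items, one sensitivity analysis and one extra line in the cost table. The downside is that some cases detected outside the trial will be added to the ILSM count. The sensitivity analysis makes that visible.
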